## 5.2 Study drug supply, dispensation, and therapeutic regimen

### 5.2.1 Drug supplies

The investigational products will be dispatched to the hospital pharmacist and delivered to the investigator, packaged and labelled in a manner appropriate to the nature of the trial, as well as in quantities and at the times necessary to enable the investigator to carry out the trial in accordance with the study protocol.

The following products will be supplied:

- Capsules of fish oil including 280mg of DHA: 3600 capsules (i.e 3 packages of 20 boxes, each box containing 60 capsules) per patient.
- Capsules of placebo: 3600 capsules (i.e 3 packages of 20 boxes, each box containing 60 capsules) per patient.

The pharmacist or the investigator will acknowledge receipt of the products supplied. He/she must ensure that they are kept under the appropriate conditions (in a secured location accessible only to study personnel, maintained below 25 °C, sheltered from light and kept dry). At the end of the study, all used and unusedstudy drugs will be fully returned to the sponsor for drug reconciliation.

### 5.2.2.Drug dispensation

1 randomisation list will be established and balanced for treatments. The treatments will be continuously numbered from 001 to 248.

At the end of the baseline evaluation, treatment numbers will be allocated to the patients in ascending order using the next available consecutive number of the list.

The first patient will so receive pack 001 , the second pack 002 and then consecutively.

The double-masked treatment will be dispensed by the investigator or the pharmacist.

3 dispensations will be done during the study:

- First dispensation on D0, at the end of the baseline visit (Visit 1).
- Second dispensation 1 year later, at the end of Visit 3 (Year 1 visit).
- Third dispensation 1 year later, at the end of visit 4 (Year 2 visit).

Each time the patient will receive a package containing 20 boxes of 60 capsules, that is to say 1200 capsules for a 1 year treatment.

Upon each dispensation, the duplicate label provided must be fixed on the corresponding case report form or on a dispensation form.

### 5.2.3 Therapeutic regimen

The patient will take 3 capsules per day: 2 capsules at noon and one capsule in the evening of either DHA (i.e. 840 mg per day : 280mg X 3) or placebo .

The capsules must be swallowed with a glass of water, during the meal.

The duration of the treatment will be 3 years.

## 5.3 Compliance with the treatment

At each visit, the patients have to bring back the empty blister-packs and the unused study medications. The compliance will be recorded in the case report form as yes or no and the frequency of forgotten capsules will be described.

The compliance will be considered to be good when 80% capsules or more are taken by the patient.

At the end of the study, all the study medications will be returned to the sponsor so that drug reconciliation can be established.

Moreover, the DHA level in serum will be a good indicator of patient compliance to treatment.

## 5.4 Randomisation and code-breaking

The randomisation list will be prepared prior to the enrolment using the QL-Ranclin software.

Treatments will be balanced in a 1 to 1 ratio.

At the end of the baseline visit (Day 0), patients who fulfilled all inclusion criteria and none of the exclusion criteria will be randomly assigned to one of the treatment groups (DHA or placebo).

Only in emergencies, and for reasons which must always be given, can the code be broken.

For this purpose sealed opaque envelopes, bearing the number of the patient and containing the name of the allocated treatment, will be given to the investigator or the pharmacist.

It is thus possible to unmask the treatment of one patient only without unmasking all the others.

## 5.5 Concomitant therapy

At each visit, information on any concomitant therapy will be collected and recorded in the case report form.

### 5.5.1 Permitted therapy

Any therapy which does not interfere with the protocol will be allowed including aspirin.

Hypolipidaemic drugs (except Maxepa and fish oil or DHA containing drugs) are allowed during the study. Their use will be recorded on the CRF and these data will be updated all along the study.

If any CNV have occurred, a suitable therapy (laser therapy or photodynamic therapy) will be performed.

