### 6.1.2 Examination schedule

The different visits will take place on D0, Month 6 (15 days), Year 1( 30 days),

Year 2 (30 days) and Year 3 ( 30 days).

Before inclusion, a baseline assessment will take place on D0. Besides validating the inclusion and exclusion criteria, this baseline visit will also enable the recording of demographic (including ethnicity) and baseline data. Data concerning some identified risk factors for AMD, as age and history of addiction to smocking, will be recorded. Moreover a diet questionnaire must be completed in order to assess the patient’s fish intake frequency.

Any general pathology (particularly diseases predisposing to bleeding or haemorrhage) and ocular pathology as well as any concomitant treatment will be recorded.

These data will be updated all along the study.

For patients previously supplemented with omega-3 fatty acids the corresponding stopping date will be recorded.

On each visit, ophthalmic assessments will include the following:

- Best corrected visual acuity measured with ETDRS charts
- Slit Lamp Examination
- Multifocal ERG (except on 6 month visit)
- Fundus photographs
- Fluorescein angiography (except on 6 month visit)

Moreover a complete profile of blood lipids will be performed on D0, at the 6 month visit and at the 3 year visit : fasting plasma lipoproteins [triglycerides (TG), total cholesterol (TC), HDL-C and LDL-C ] and fatty acids in serum and in red blood cell membranes (RBCM) will be measured. To this end 15 ml of venous blood will be collected after a 12 hour fasting period (as described in appendix I.D).

These data will allow first to evaluate for each patient the compliance to the treatment (DHA level in plasma) and the efficacy of DHA to penetrate the cell membrane (DHA level in RBCM), then to confirm the safety of the treatment concerning the metabolism of lipoproteins (fasting plasma lipoprotein profile).

Moreover since TC is considered as a risk factor for age-related macular degeneration, it will be considered for evaluation of treatment efficacy.

Furthermore, as previously mentioned (see section 4.2), apoE genotype of consenting patients will be evaluated on DNA of white blood cells, on D0.

10 ml of venous blood will be collected. The protocol for extraction of DNA from white blood cells and for evaluation of apoE allele is given in appendix I.E. If appropriate, the efficacy of the treatment will be assessed considering the apoE genotype .

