### 6.2.2 Systemic tolerance

Fasting plasma lipoproteins profile [triglycerides (TG), total cholesterol (TC), HDL-C and

LDL-C] will be performed on D0, at the 6 month visit and at the 3 year visit. To this end blood samples after fasting will be taken. The protocol for dosage is described in appendix I.D. If any abnormality is noticed which was either not present at baseline or which was worse than at baseline, then the investigator will have to complete an adverse event form .

Moreover, all systemic adverse events, particularly digestive adverse events (nausea, eructations, diarrhea or abdominal pain) and bleeding events*, will be registered all along the study (see paragraph 6.2.3).

** because there is no simple, specific and accurate biologic index allowing to predict the risk for bleeding.*

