At each follow-up visit, the percentage of patients with changes (from the previous assessment) in the slit lamp examination will be compared between groups by means of a CHI square test or a Fisher test .

Change from baseline in profile of plasma lipoproteins will be compared between groups using a Student t-test or a Wilcoxon Rank Sum test depending on data normality.

Adverse or unexpected events will be counted and described by visit. In case of a sufficient number of adverse events, the percentage of patients having at least one adverse event will be compared between the 2 groups by means of a CHI square test. In case of serious adverse events, these will be counted and described completely and the corresponding patient profile will be detailed.

Other variables

The comparability of quantitative parameters between groups on D0 will be analysed by a Student t-test or a Wilcoxon Rank sum test depending on data normality. Qualitative parameters will be analysed by a CHI square test or a Fisher test depending on the number of patients in classes.

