## 8.2 Determination of sample size

The primary criterion is the time to occurrence of choroidal new vessels (CNV) in the study eye.

The occurrence rates of CNV in both treatment groups will be compared using a log-rank test.

According to previous studies (24) the 3 year risk of developing CNV in one eye is about 30 % (10% per year) for patients with CNV in the fellow eye.

Based upon expectation that DHA-treatment should reduce this rate to 15% at 3 years after D0 , sample size was thus performed assuming a 3 year CNV risk for the study eye in the treated group and in the placebo group to be 15% and 30% respectively.

The number of patients has been calculated with the Pass software for survival curves according to the following hypotheses:

- 2 tailed test
- Type I error  = 0.05
- Type II error  = 0.20 (80% power)
- Regular recruitment and Inclusion period: 1 year
- Follow up period per patient : 3 years
- Equal proportion of patients in each treatment group
- Drop-out rate in each group : 20%

Based on the above specifications the total number of patients should be 245.

Data on 248 evaluable patients are to be available (124 per group).

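### The year-3 lipid safety comparison takes no account of hypolipidaemic drugs started after D0, so any effect of the capsules on lipids may be diluted there

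*Protocol*

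**What the plan says.** The fasting lipoprotein profile (triglycerides, total cholesterol, HDL-C, LDL-C) is a named safety variable. Section 6.1.2 gives its purpose: "then to confirm the safety of the treatment concerning the metabolism of lipoproteins". Sections 6.1.2 and 6.2.2 and the flow chart in 6.3 schedule it at D0, month 6 and year 3 only.

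On lipid-lowering treatment, section 5.5.1 says "Hypolipidaemic drugs (except Maxepa and fish oil or DHA containing drugs) are allowed during the study" and continues "Their use will be recorded on the CRF and these data will be updated all along the study". No stable-dose, timing or start condition is attached.

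On individual results, section 6.2.2 requires an adverse event form "If any abnormality is noticed which was either not present at baseline or which was worse than at baseline".

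On analysis, section 8.1 (safety variables) says "Change from baseline in profile of plasma lipoproteins will be compared between groups using a Student t-test or a Wilcoxon Rank Sum test", the choice depending on normality. It names no covariate, stratum or rule for lipid-lowering drugs. Section 8.1 lists concomitant medication only as something to be recorded.

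**The concern.** Whether a patient starts a lipid-lowering drug can depend on the endpoint being compared. The duty to report a worsened profile implies that the month-6 result reaches the investigator, and treatment may follow. If the capsules raise a lipid fraction, more patients in that arm would be expected to start treatment. If they lower one, as the Introduction expects for triglycerides, more placebo patients would. In both cases the year-3 difference moves towards zero.

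Year 3 is the only scheduled lipid measurement after month 6, so it alone covers the last 30 of 36 months of exposure. A small difference there could mean that the capsules have little effect, or that they have an effect that was partly treated away. The planned test cannot tell these apart. The CRF data on drug use that would help are not assigned to any analysis in section 8.1.

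**Working it through.** **What the Protocol supplies.** It states no expected lipid effect, variability, start rate or drug effect. The sample size in section 8.2 rests on 3-year risks of choroidal new vessels ("treated group and in the placebo group to be 15% and 30% respectively") and has no bearing on lipids beyond fixing the number of patients. With 124 per group and 20% drop-out, 124 × 0.80 = 99.2, or about 99 per arm at year 3.

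**General relation.** If starting the drug lowers a patient's value by *e*, and start rates are *q1* (DHA) and *q0* (placebo), then

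observed year-3 difference = true difference − (*q1* − *q0*) × *e*.

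**Assumptions for a range (none from the Protocol).** Lipid SD is 1 and the correlation between visits is 0.7. A drug is started when the month-6 value exceeds the baseline mean by more than 1 SD, by 50% or 100% of such patients. It lowers year-3 values by 1.0 or 1.5 SD. The true adverse difference is 0.2 to 0.4 SD. The test is a t-test on change from baseline with 99 per arm, in 4,000 simulated trials per setting.

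**Hand check of one setting.** For a true difference of 0.3 SD, a drug effect of 1.0 SD and all eligible patients treated, simulated start rates are 24.2% and 15.9%. The shift is (0.242 − 0.159) × 1.0 = 0.083. The simulated difference without starts is 0.299, and 0.299 − 0.083 = 0.216, which matches the simulation.

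**Selected results.** "Kept" is the year-3 difference with starts divided by that without.

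| True diff. (SD) | Drug effect (SD) | Share treated | Start rates, DHA vs placebo | Year-3 diff. without → with starts | Kept | Year-3 power without → with starts | Month-6 power |
|---|---|---|---|---|---|---|---|
| 0.2 | 1.0 | 50% | 10.7% vs 7.9% | 0.199 → 0.173 | 87% | 44% → 31% | 45% |
| 0.3 | 1.0 | 50% | 12.0% vs 7.9% | 0.299 → 0.255 | 85% | 78% → 57% | 76% |
| 0.3 | 1.0 | 100% | 24.2% vs 15.9% | 0.299 → 0.216 | 72% | 78% → 42% | 77% |
| 0.3 | 1.5 | 50% | 12.0% vs 7.9% | 0.301 → 0.239 | 79% | 78% → 47% | 78% |
| 0.3 | 1.5 | 100% | 24.2% vs 16.0% | 0.301 → 0.178 | 59% | 78% → 25% | 77% |
| 0.4 | 1.5 | 100% | 27.4% vs 15.9% | 0.398 → 0.229 | 58% | 95% → 36% | 95% |

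Over all settings run, 58% to 87% of the true difference is kept, so 13% to 42% is lost. Month-6 power does not move because these starts follow the month-6 sample.

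**What baseline adjustment does.** With a correlation of 0.7, the variance of a change score is 2 × (1 − 0.7) = 0.60. The residual variance after adjustment for the D0 value is 1 − 0.7² = 0.51. The ratio is 0.51 / 0.60 = 0.85, so adjustment removes 15% of the variance. That sharpens both comparisons and handles chance imbalance at D0. It does not undo the effect of later drug starts, so the start rates have to be reported as well.

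**The case against.** The strongest reply is that the Protocol is silent rather than wrong. Nothing in section 8.1 says that lipid values are used whatever drugs have been started. The handling of concomitant drugs in a safety laboratory summary is often left to the statistical analysis plan, which is not shown. A randomised year-3 comparison that includes usual concomitant care is also a legitimate quantity. This stands, and it keeps the point minor. However, section 8.1 does name the variable, the contrast and the tests. Where it wants covariates, as for the primary analysis, it lists them.

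A reader might infer that lipid harm could be hidden from the trial. The documents do not support that. The month-6 comparison precedes any start prompted by the month-6 result, and section 6.2.2 sends each new or worse abnormality to an adverse event form. The second route is weaker than it looks: section 8.1 counts and describes events by visit but formally compares only the percentage of patients with at least one event, and only if events are numerous enough. No lipid-specific event comparison is stated.

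A reader might also infer that the plan would take a null result as proof of lipid safety. Section 6.1.2 gives a purpose for the measurement; no passage gives such a decision rule.

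Finally, lipid harm is not what the Protocol expects: the Introduction anticipates higher HDL and lower triglycerides. The dilution applies equally to a favourable effect.

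**Conclusion.** The point holds as a minor gap in an analysis that the Protocol does specify. Unrestricted starts, a month-6 result known to the investigator and an unadjusted year-3 test together allow an effect on lipids to be diluted at year 3. The loss of about 13% to 42% is an illustration. It depends on the assumed start rule, drug effect, visit correlation and true difference, and the Protocol fixes none of them. If the capsules do not affect lipids, starts prompted by lipid results should not differ systematically by arm and the mechanism disappears. The month-6 comparison is largely unaffected and the primary log-rank analysis is untouched. The documents give no ground for calling the permitted-therapy rule itself an error.

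**What to change.** In section 8.1, under safety variables:

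- Compare between arms the percentage of patients who start or intensify a hypolipidaemic drug after D0, using the CRF data already collected under section 5.5.1, and report it beside the year-3 lipid result.
- Adjust the month-6 and year-3 lipid comparisons for the D0 value and for hypolipidaemic use at D0. Do not adjust for use after D0, which treatment may itself influence.
- State that the year-3 result is interpreted together with the month-6 result and the start rates.

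Replacing values after a drug start by the last earlier value is tempting but should not be adopted. With three sampling times, that value can only be from D0 or month 6. A D0 value sets the change to exactly zero; a month-6 value may be up to 2.5 years old and carries forward the high reading that prompted treatment. It also sits badly with the statement in section 8.1 that missing data are not extrapolated.

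The cost is one extra table and a few lines of text. No new data are needed, and the permitted-therapy rule and the primary analysis stay as they are.

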### 5.5.2 Prohibited therapy

Therapies interfering with the protocol are prohibited during the study except if absolutely necessary for the patient’s care:

- Anticoagulants
- Treatment with Maxepa or omega-3 polyunsaturated fatty acids
- Treatment with alpha-tocopherol acetate
- Any concomitant nutritional supplementation (including supplementation with fish-oil or omega-3 fatty acids and alpha-tocopherol acetate/vitamin E).

# 6. EFFICACY AND SAFETY VARIABLES

## 6.1 Efficacy

### 6.1.1 Evaluation criteria

Primary criterion:

Choroidal neovascularization heralds the onset of exudative macular degeneration, the most severe stage of the disease.

Since this study is designed to evaluate the efficacy of an oral DHA supplementation in the prevention of exudative macular degeneration it is justified to choose the time to occurrence of CNV in the study eye as the main criterion in this study.

The study eye will be the eye not affected with CNV before entering the study.

Secondary criteria:

The ocular criteria will concern systematically the study eye.

- Percentage of patients for whom new vessels occur during the study,
- Change from baseline in visual acuity in LogMar units (ETDRS) and proportion of patients with a visual acuity decrease from baseline of more than 15 letters at ETDRS,
- Change from baseline in visual function (assessed with a multifocal ERG),
- Occurrence and progression of drusen (number, size, and area) ,

all criteria allowing to determine the efficacy of the treatment to slow-down the progression of the disease.

- DHA concentration changes in red blood cell membrane is a surrogate marker for DHA ability to penetrate the retina visual cells.

### 6.1.2 Examination schedule

The different visits will take place on D0, Month 6 (15 days), Year 1( 30 days),

Year 2 (30 days) and Year 3 ( 30 days).

Before inclusion, a baseline assessment will take place on D0. Besides validating the inclusion and exclusion criteria, this baseline visit will also enable the recording of demographic (including ethnicity) and baseline data. Data concerning some identified risk factors for AMD, as age and history of addiction to smocking, will be recorded. Moreover a diet questionnaire must be completed in order to assess the patient’s fish intake frequency.

Any general pathology (particularly diseases predisposing to bleeding or haemorrhage) and ocular pathology as well as any concomitant treatment will be recorded.

These data will be updated all along the study.

For patients previously supplemented with omega-3 fatty acids the corresponding stopping date will be recorded.

On each visit, ophthalmic assessments will include the following:

- Best corrected visual acuity measured with ETDRS charts
- Slit Lamp Examination
- Multifocal ERG (except on 6 month visit)
- Fundus photographs
- Fluorescein angiography (except on 6 month visit)

Moreover a complete profile of blood lipids will be performed on D0, at the 6 month visit and at the 3 year visit : fasting plasma lipoproteins [triglycerides (TG), total cholesterol (TC), HDL-C and LDL-C ] and fatty acids in serum and in red blood cell membranes (RBCM) will be measured. To this end 15 ml of venous blood will be collected after a 12 hour fasting period (as described in appendix I.D).

These data will allow first to evaluate for each patient the compliance to the treatment (DHA level in plasma) and the efficacy of DHA to penetrate the cell membrane (DHA level in RBCM), then to confirm the safety of the treatment concerning the metabolism of lipoproteins (fasting plasma lipoprotein profile).

Moreover since TC is considered as a risk factor for age-related macular degeneration, it will be considered for evaluation of treatment efficacy.

Furthermore, as previously mentioned (see section 4.2), apoE genotype of consenting patients will be evaluated on DNA of white blood cells, on D0.

10 ml of venous blood will be collected. The protocol for extraction of DNA from white blood cells and for evaluation of apoE allele is given in appendix I.E. If appropriate, the efficacy of the treatment will be assessed considering the apoE genotype .

### 6.1.3 Assessments of efficacy variables

### Primary efficacy variable

The occurrence of choroidal new vessels in the study eye will be determined from prospective assessment of fluorescein angiography every year.

Patients will be asked to report any new visual symptoms referable to the study eye between visits and to come back immediately for an angiography. Then a suitable laser or photodynamic therapy will be performed if any CNV have occurred.

Fluorescein angiography will allow to detect the presence and specify the location (extrafoveal, juxtafoveal, subfoveal), type (classic, occult) of CNV. It will be performed, through the dilated pupil, after intra-venous injection of 10% sodium fluorescein. This examination will be performed first on D0 for both eyes, then yearly.

If CNV are suspected in the study eye, an indocyanine green (ICG) angiography will be also performed to confirm their occurrence and characterize them precisely.

The protocol for fluorescein and ICG angiography is described in appendix I.C.

### Secondary efficacy variables

Fundus photographs (red free frame), performed through the dilated pupil, will allow :

- first to describe the type, number, size and area of drusen on D0,
- then to evaluate the occurrence and progession of drusen (number, size and area), in the study eye, at each follow-up visit.

For this purpose, an automatic quantification of drusen will be performed by LERISS laboratory using an image enhancement and automatic detection and quantification of drusen software. The protocol for quantification and evaluation of evolution of drusen is described in appendix I. B.

Change in visual acuity will be evaluated from baseline using the ETDRS charts. Best corrected visual acuity will be evaluated, before pupil dilatation, by the same person at each visit. The protocol for evaluation of visual acuity is given in appendix I. A.

A significant decrease in visual acuity is defined as a decrease of more than 15 letters at ETDRS.

Multifocal ERG modification from baseline will be evaluated yearly on the study eye. ERG responses will be obtained from the anesthetized cornea, through the dilated pupil, with a bipolar contact lens electrode (see appendix I.G). ERG must be performed before fundus photographs and angiography.

DHA concentration in red blood cell membranes (RBCM) will be performed on D0, at the 6 month visit and at the 3 year visit. For this purpose, 5 ml of 12 hour fasting blood samples will be taken in the early morning. DHA concentration change in red blood cell membrane is considered as the witness of the DHA ability to penetrate the retina visual cells*.* The protocol for dosage of fatty acids in RBCM is given in appendix I.D.

